### Randomization

After information is relayed by the physicians of the local clinic, the legal guardians and the child who wishes to participate must give oral consent. Online-based randomization is provided by the Interdisciplinary Center for Clinical Trials (IZKS), University Medical Centre of Mainz, and detailed information of the individual branch (operative or conservative) is given. All patients/caregivers, which are possible candidates for the trial, are informed about the aim of the trial, the possibility of conservative and operative treatment, the workflow and the randomization procedure. Written informed consent will be obtained from parents and patients before inclusion.

### Observer blinding

The person (usually a doctor) who determinates the Cooney score after 3, 12 and 24 months should not participate in the treatment of the patient and should not know which procedure was performed. In addition, available x-rays will be analyzed centrally to minimize bias.

### Trial schedule

For an overview of the schedule see Fig. 2.

**Fig. 2 Fig2:**
[figure not shown]
Work flow

Children between 5 and 11 years come to the emergency department with angulated fractures of the forearm. If all criteria are fulfilled and informed consent is given, the patient will be randomized.

After inclusion into the trial, dependent on the randomization result, patients are treated conservatively with a plaster (experimental group/group 1) or prepared for reduction and osteosynthesis under anesthesia (control group/group 2). A cast similar to the experimental group is applied.

For both groups, the kind of cast used (upper arm, forearm, sandwich, cast, or plaster of Paris) does not influence outcome of bony healing. In all controls, physical examinations in order to rule out complications of cast and serious adverse events are performed.

Patients included into the experimental group (1) go home after their treatment and come back the next day for clinical control. At this time-point quality-of-life questionnaires (ZUF-8 and CHC-SUN modified) are handed out. After 7 days, a clinical and X-ray control are performed in order to rule out secondary dislocation. If there is uneventful course of treatment, the next visit will be 4 weeks later for the next clinical and radiological control. If complete healing of the fracture is achieved, the cast is removed. Once again quality-of-life questionnaires are handed-out. Patients begin movements of daily routine, and physical exercise is postponed for another 2 to 4 weeks.

Patients included in the control group (2) stay on the ward after the operation for 1 or 2 days. Parents are instructed how to clean pin(s) or to perform wound controls. Exact reduction and position of K-wires is documented either during the procedure or on the next day. Quality-of-life questionnaires are handed out. At the next visit 4 weeks later radiological control and pin removal are performed, so far bony healing is documented. Patients begin with movements of daily routine, and physical exercise is postponed for another 2 to 4 weeks. The next quality-of-life questionnaires are handed out.

Three months after trauma, a next clinical control as well as assessment of the Cooney score and quality of life (CHC-SUN and ZUF-8) is conducted [5, 11]. 12 and 24 months after trauma similar visits in order to assess the same parameters are scheduled.

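### Between the first days and the 4-week visit only the cast arm has a scheduled examination, so minor complications are likely to be less completely captured in the pinned arm

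*Protocol article*

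**What the plan says.** The Trial schedule section (text following Fig. 2) describes early follow-up arm by arm.

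- **Cast arm (group 1).** Children "go home after their treatment and come back the next day for clinical control". Next: "After 7 days, a clinical and X-ray control are performed in order to rule out secondary dislocation". If the course is uneventful, "the next visit will be 4 weeks later for the next clinical and radiological control".
- **Pinned arm (group 2).** Children "stay on the ward after the operation for 1 or 2 days". On imaging: "Exact reduction and position of K-wires is documented either during the procedure or on the next day". On care at home: "Parents are instructed how to clean pin(s) or to perform wound controls". Then: "At the next visit 4 weeks later radiological control and pin removal are performed, so far bony healing is documented".

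The same section states that, at every control in either group, the child is physically examined for cast complications and serious adverse events. It also says that the pinned arm receives a cast similar to that of the other arm. From 3 months on, the visits are the same in both arms.

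Safety is a secondary objective (Secondary objective). Complications graded by Dindo-Clavien, second reduction and reapplied K-wire osteosynthesis are secondary endpoints (Secondary endpoint). The Safety section has serious events reported within 24 hours of being observed, and has therapeutic complications documented and analysed.

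**The concern.** When events are found by examining the child, the arm that is examined more often yields more recorded events at the same true risk. Here the article itself fixes both the detection rule and the unequal number of examinations.

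Both arms wear a cast, so cast problems can occur in both, yet around day 7 they are looked for in one arm only. Pin and wound problems belong to the pinned arm. Many would arise while the parents look after the pins and no control is scheduled, and those that settle before week 4 may leave no record.

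The complication comparison is at stake, and the Discussion relies on it when it speaks of remodeling as a possibly safe alternative. An analysis plan cannot recover events that were never recorded.

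**Working it through.** **1. Schedules side by side** (treatment = day 0)

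| Period | Cast arm | Pinned arm |
|---|---|---|
| First days | clinical control on day 1 | ward for 1 or 2 days, wire position documented |
| About day 7 | examination and film | nothing scheduled |
| 4-week visit | examination and film | film and pin removal |
| 3, 12, 24 months | same visits | same visits |

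The ward stay is a fair match for the day-1 control. The unmatched item is one examination with one film: 1 against 0 between the first days and the 4-week visit.

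**2. When the 4-week visit falls.** The text does not say from which day the 4 weeks are counted.
- Cast arm: day 28 from treatment, or 7 + 28 = day 35 from the day-7 control. The Treatment section gives 4 weeks of plaster for this arm, so the two passages need to be reconciled.
- Pinned arm: day 28 from the operation, or day 29 or 30 from discharge.

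The period that the visit looks back on could therefore differ by up to 35 − 28 = 7 days between arms. A complication history taken there needs a common cut-off day.

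**3. Direction.** Let t_c and t_p be the true complication rates (cast, pinned) and s_c and s_p the shares recorded. The observed difference, cast minus pinned, is t_c·s_c − t_p·s_p. If the extra control makes s_c larger than s_p, then with equal true rates the difference is shifted upwards, against the cast arm. If pinning truly causes more minor problems, part of that excess is hidden. Both routes make the cast arm look relatively worse.

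**4. Size.** The article states no complication rate and no capture share, so there is no figure to reproduce. As an illustration, take equal true rates t, s_c = 1 and s_p = s. The spurious difference is t × (1 − s). The last column is the chance of a two-sided p < 0.05 against the cast arm with 371 per arm (Number of patients). Without differential capture it would be 2.5 %.

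| Assumed t | Assumed s | Difference, points | Chance of p < 0.05 against cast |
|---|---|---|---|
| 5 % | 0.9 | 0.5 | 5 % |
| 5 % | 0.8 | 1.0 | 10 % |
| 5 % | 0.5 | 2.5 | 43 % |
| 10 % | 0.9 | 1.0 | 7 % |
| 10 % | 0.8 | 2.0 | 16 % |
| 10 % | 0.5 | 5.0 | 74 % |
| 20 % | 0.9 | 2.0 | 10 % |
| 20 % | 0.8 | 4.0 | 29 % |
| 20 % | 0.5 | 10.0 | 97 % |

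At t = 10 % and s = 0.5, the unrecorded events number 371 × 0.05 = 18.55, about 19 children.

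The lower values of s are demanding. If a fraction f of all complications falls in the interval and a fraction m of those is lost in the pinned arm only, then s = 1 − f·m. So s = 0.5 needs f·m = 0.5: half of all complications would have to fall in these weeks and also go unrecorded. For s = 0.9, f·m = 0.1 is enough.

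**The case against.** **Different treatments need different follow-up.** This stands, and nothing here asks for another visit or film.

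**Events surface without a visit.** Serious events are reported when observed, and a child with a troublesome pin or cast will be brought in. This largely stands for serious and clearly symptomatic events. It does not cover minor or passing ones, which a graded classification is meant to include.

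**Form content belongs in the full protocol or case report form.** This stands in part: the full protocol may already ask about the interval since discharge, and the point would then largely fall away. But it does not rest on silence. The article states that detection is by examination at controls, and states that the controls differ.

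**Fig. 2 is not shown.** It might list a further contact. The text calls the 4-week control the next visit, so such a contact would have to be reconciled with it.

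**Stronger readings that the documents do not support:**
- *Early displacement is over-detected in the cast arm and distorts an endpoint.* Malalignment is an endpoint at 12 and 24 months, on visits common to both arms. Early displacement is not listed.
- *Re-interventions prompted by the day-7 film are artefacts.* The film is part of the cast strategy, so a second reduction that follows from it is a real consequence and belongs in the comparison.
- *Cast problems in the first week are sought in the cast arm only.* Pinned children are inpatients, in a cast, for the first 1 or 2 days.

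**Conclusion.** The point holds for a secondary safety comparison. One scheduled examination with film in the cast arm has no counterpart in the pinned arm, while complications are sought at scheduled controls. Capture of minor or passing events in those weeks is therefore likely to be less complete in the pinned arm, mainly to the disadvantage of the cast arm.

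The size is unknown. Differences of 0.5 to 10 points follow only from the assumed rates and capture shares. The upper end needs heavy loss, and mild loss is nearly harmless. The article states no test or margin for complications, so the chances shown are only a yardstick.

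A reader might infer that the safety comparison is uninterpretable in both directions. The text does not support that: the identified mechanisms push mainly one way, so a favourable safety result for casting would be conservative, while an apparent excess of minor complications under casting would be hard to read. A reader might also infer that the primary endpoint is biased. Its 24-month assessment is scheduled alike in both arms and made by an observer who should not know the treatment, so the unequal early visits do not affect it.

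**What to change.** Leave both care schedules as they are and equalise the recording.

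1. At the 4-week visit in both arms, complete the same structured complication history for the whole period since treatment, up to a common cut-off day counted from treatment. It should cover cast problems, wound or pin problems, unscheduled visits and treatment elsewhere.
2. Base the between-arm complication comparison on this history plus the later visits.
3. Keep every re-intervention in the comparison. Flag complications and re-interventions first found at the scheduled day-7 control, and show the comparison with and without them.
4. State the day from which each arm's 4 weeks are counted, so that the schedule agrees with the Treatment section.

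The cost is one case report form page at a visit that both arms already attend, and one extra display in the analysis. The downside is recall over about 4 weeks. At submission 42 of the planned 742 patients were included (Trial status), leaving 742 − 42 = 700 for whom the form could have been in place from the start.

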### Quality assurance

Clinical on-site monitoring in all trial centers is done by personal visits of clinical monitors according to the standard operating procedures of the IZKS. The monitor will check the informed consent forms and will review the entries into the case report form (CRF) on the basis of source documents. The physician allows the monitor access to all essential documents and provides support to the monitor. The IZKS Mainz assists the physician in conducting the study according to the protocol, as well as to meet regulatory and ethical requirements.

### Data management

Data management will be done by the IZKS. All participating clinics will enter their collected information in the CRF. Data will be exported into the statistical analysis system and checked for plausibility, consistency and completeness. Any missing data or inconsistencies will be reported back to the respective site and clarified by the responsible investigator. All collected data will be processed according to the German Data Protection Law and handled in strictest confidence.

### Power calculation/analysis

All patients presenting a Cooney Score of at least 90 after 24 months and, if clinically obvious, a radiologic displacement not exceeding 5°, will be compared between treatment groups by calculating a one-sided 97.5 % confidence interval of the difference of rates according to Farrington and Manning [9]. If this interval is located completely above the noninferiority bound of -5 %, noninferiority of the experimental intervention will be claimed. The primary analysis population is the per-protocol population, comprising all randomized patients without major protocol violations and at least one Cooney score radiological displacement measurement after intervention.

The primary endpoint is the validated Cooney-Score. This score considers subjective (pain, strength, activity before and after trauma) as well as objective (range of motion) parameters and has been validated in several trials that also included children and adolescents. As it is assumed that differences between the treatment groups with respect to the Cooney Scores fully disappear at (and not clearly before) 2 years after surgery/immobilization, an earlier time was not chosen for primary analysis.

Cooney Scores will be calculated according to the standard approach of aggregating the single items.

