### Inclusion criteria

Patients meeting all of the following criteria will be considered for admission to the trial:Age 5 to 11 yearsDistal metaphyseal fracture of radius or complete distal metaphyseal forearm fracture23-M/2-3 or 23-E/1-2 (according to AO classification)Angulated radius or complete forearm fractures in the distal third of the boneAngulated physiolysis with or without wedge of the metaphysisAngulation up to 30°Age 5 to 7 years 15°-30°Age 8 to 11 years 10°-25°Informed consent of child and parents

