### Number of patients

A total of 742 patients shall take part, with 371 per group. Recruiting is planned for 30 clinics.

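### The primary rate difference leaves out age and initial angulation; this is valid, but it forgoes a probable small precision gain and a partial correction of imbalance in the per-protocol set

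*Protocol article*

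**What the plan says.** All references are to the Protocol article.

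- **Endpoint (Power calculation/analysis).** A child counts as a success with "a Cooney Score of at least 90 after 24 months and, if clinically obvious, a radiologic displacement not exceeding 5" degrees.
- **Method (same section).** Success rates are compared by a "one-sided 97.5 % confidence interval" for the "difference of rates according to Farrington and Manning", against a "noninferiority bound of -5" percentage points. No covariate or stratum is named.
- **Analysis set (same section).** "The primary analysis population is the per-protocol population": randomised children without major protocol violations and with a post-treatment measurement.
- **Size (Number of patients).** "A total of 742 patients shall take part, with 371 per group".
- **Entry data (Inclusion criteria).** Angulation limits depend on age: "Age 5 to 7 years 15°-30°Age 8 to 11 years 10°-25" degrees. Both values must be known before a child can be randomised.
- **Randomization.** Allocation is online. The section states no stratification factor.

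**The concern.** Two baseline variables are available for every child at no cost. The age-specific angulation limits show that the protocol treats them as jointly relevant, and the Background section links correction of the axis to growth. Initial angulation also bears on the endpoint, which includes a displacement limit where malalignment is clinically obvious, and in Group 1 the angulation is left unreduced.

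Two things are at stake. First, an interval that ignores prognostic baseline variables tends to be somewhat wider than it need be. Second, the primary set is formed after randomisation, so balance on these variables is not guaranteed in it. If more severely angulated children left Group 1 preferentially, the crude difference would move towards a non-inferiority claim, and a crude interval cannot correct for that.

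**Working it through.** **Inputs.** From the article: margin 5 points, one-sided 2.5% error, Farrington-Manning method, 371 per group. Assumed, because the article does not give them: success rates, power, loss, prognostic strength and pattern of exclusions.

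**1. The plan's sample size.** Assume 95% success in both arms, 80% power and 10% loss.

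- Alternative: s1 = √(2 × 0.95 × 0.05) = 0.3082.
- Null (restricted maximum-likelihood rates 0.9151 and 0.9651): s0 = √(0.9151 × 0.0849 + 0.9651 × 0.0349) = 0.3337.
- n = [(1.960 × 0.3337 + 0.8416 × 0.3082) / 0.05]² ≈ 334 per arm, and 334 / 0.9 = 371.1.

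So 742 fits an unadjusted Farrington-Manning design under these assumptions. This shows consistency only, since the inputs are not stated.

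**2. Precision.** Adjusted variance ≈ crude variance × (1 − R²), where R² is the share of outcome variance explained by age and angulation. At 95% success and 371 per arm, the crude half-width is 1.96 × √(2 × 0.95 × 0.05 / 371) = 3.14 points. Power below uses the simple unpooled variance.

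| R² | Half-width (points) | Power | Equivalent total N, 742 × (1 − R²) |
|---|---|---|---|
| 0% | 3.14 | 87.8% | 742 |
| 1% | 3.12 | 88.1% | 735 |
| 2% | 3.10 | 88.4% | 727 |
| 5% | 3.06 | 89.4% | 705 |
| 8% | 3.01 | 90.3% | 683 |
| 10% | 2.98 | 90.9% | 668 |

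Which R² is plausible has to be assumed:

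- Two equal halves with success 93% and 97%: R² = 0.02² / (0.95 × 0.05) = 0.8%. With 91% and 99%: 0.04² / 0.0475 = 3.4%.
- One combined predictor with odds ratio 1.5 to 3 per SD: 0.8% to 7.1% at 5% failure, and 1.5% to 11% at 10% failure.
- Simulation, 334 per arm, about 94% success, two covariates with log-odds 0.3, 0.5 and 0.8 per SD each: variance falls about 1%, 2% and 4%, and power rises 0.4, 1.0 and 1.9 points. A further simulation at 334 per arm gave about 0% to 8% of variance.

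**3. Imbalance.** Shift in the crude difference = difference in the share of high-risk children × risk gap.

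- Chance alone: SD of the share difference = √(2 × 0.25 / 334) = 3.9 points. With a gap of 4 to 10 points the shift is about 0.2 to 0.4 point, which the interval already covers.
- Systematic (assumption: 10% of Group 1 excluded, all from the high-angulation half, none from Group 2): the high-angulation share falls from 50% to 40/90 = 44.4%, or 5.6 points. With failure 2% and 8% by half, the shift is 5.56% × 6 = 0.33 point. With 5% and 20%, it is 5.56% × 15 = 0.83 point. These are 7% and 17% of the margin.

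**4. How much adjustment removes.** Same exclusions, true difference zero, logistic model with arm and angulation half, standardised over the analysis set. Each cell gives the bias for failure 2%/8% and then 5%/20%.

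| Scenario | Crude bias (points) | Adjusted bias (points) |
|---|---|---|
| Same gap in both arms, exclusion unrelated to outcome within a half | 0.33; 0.83 | 0; 0 |
| Angulation prognostic in Group 1 only | 0.33; 0.83 | 0.18; 0.44 |
| Excluded children at twice their half's risk | 1.2; 3.1 | 0.9; 2.4 |

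For the third row at 2%/8%, the remaining high-half risk is (0.5 × 8 − 0.1 × 16) / 0.4 = 6%. Group 1 then fails at (0.5 × 2 + 0.4 × 6) / 0.9 = 3.8% against 5% in Group 2. About three quarters of that bias survives adjustment.

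**The case against.** The case for leaving the plan alone is strong in several respects.

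- **Validity.** Under randomisation the crude interval is valid, and 742 is compatible with it. This stands. A reader might infer that the primary method is wrong or the sample size mis-stated; nothing in the article supports either.
- **Condensed article.** Stratification factors and adjusted sensitivity analyses may be in the full protocol or SAP. This stands for sensitivity analyses. It does not remove the point, because the article states the primary method outright and that method is crude.
- **Prognostic strength.** No figure is given. Each age band spans only 15 degrees, and Group 2 is reduced and pinned, so initial angulation may predict outcome mainly in Group 1. This stands, and the precision gain could be close to nil.
- **Exclusions.** The scenario is one-sided, and the article does not define a major violation. Second reduction and repeat wiring are secondary endpoints, so such children may well be retained. Against this, a child who needs treatment outside the protocol is discontinued, and the 7-day X-ray for secondary dislocation is described for Group 1 only. Differential loss is therefore possible but not shown.
- **Remedy.** A reader might also infer that adjustment would repair the per-protocol comparison. It would not: children who displace are probably at higher risk than others with equal angulation, and step 4 shows how much bias then remains.

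**Conclusion.** The point holds as a worthwhile improvement and not as the correction of an error. The primary analysis is unadjusted although two plausibly prognostic variables are known for every child.

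The probable precision gain is small: roughly 0% to 8% of variance near 95% success, worth up to a few power points. The range rests on assumed prognostic strengths; 11% is reached only at an assumed 10% failure rate and an odds ratio of 3 per SD.

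For the per-protocol set, adjustment removes only the imbalance that measured age and angulation explain. The shift of 0.3 to 0.8 point depends on an assumed one-sided exclusion. It is removed in full only if the risk gap is the same in both arms and exclusion is uninformative within angulation levels. Selection into the set after randomisation would remain a separate matter.

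**What to change.** In Power calculation/analysis, prespecify before unblinding that the primary estimate is a risk difference adjusted for age and initial angulation, plus any factor used to stratify the randomisation. Either of these would serve:

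- a marginal risk difference standardised from a logistic model with arm, age and angulation (both continuous), with a delta-method or bootstrap lower bound and the standardisation population named; or
- a Farrington-Manning or Miettinen-Nurminen interval stratified by age band and angulation.

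Both keep the risk-difference scale. Compare the one-sided 97.5% lower bound with the same -5 point margin, and keep the crude interval as a sensitivity analysis. The text should not present the adjustment as a remedy for per-protocol selection.

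**Cost.** About one sentence, with no new data, patients or margin. The downside is a slightly more complex model with few events: at an assumed 5% failure rate and 668 evaluable children there are about 0.05 × 668 = 33 failures. That supports three terms, but a penalised or stratified fallback should be named in case there are fewer. It has to be fixed in advance, because adjustment chosen after an imbalance is seen would carry little weight.

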### Treatment

Group 1 (experimental/conservative): Plaster immobilization without any reduction for 4 weeks, the kind of plaster (Paris, cast, forearm, upper arm or sandwich) is to be determined by the treating clinic. As no reduction is performed, no anesthesia is needed. After the fracture is immobilized with the plaster, the patient will leave the emergency department.

Group 2 (control): Closed reduction under anesthesia, percutaneous K-wire osteosynthesis with one or two wires (through physis or Kapandji), plaster (Paris, cast, forearm, upper arm or sandwich) is to be determined by the treating clinic. No other form of osteosynthesis is allowed. After the operation, the patient is treated on the ward for 1 or 2 days.

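### Non-inferiority can be claimed on the per-protocol set alone, which leaves the test open to bias towards success if cast-arm children who are later reduced or pinned are excluded and do worse than the rest

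*Protocol article*

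**What the plan says.** All places are in the protocol article.

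- **Analysis set** (Power calculation/analysis): "The primary analysis population is the per-protocol population, comprising all randomized patients without major protocol violations", with the further condition of "at least one Cooney score radiological displacement measurement after intervention". The article names no analysis of all randomised children that must agree before the claim is made.
- **Claim rule** (same section): a "one-sided 97.5" % Farrington-Manning confidence interval for the difference in success rates, with non-inferiority claimed if it lies "completely above the noninferiority bound of -5" %.
- **Success** (same section): "All patients presenting a Cooney Score of at least 90 after 24 months and, if clinically obvious, a radiologic displacement not exceeding" 5°. A later reduction or pinning is not itself a failure under this definition.
- **Experimental arm** (Treatment): "Plaster immobilization without any reduction for 4 weeks".
- **Discontinuation criteria**: one reason for discontinuing a child is the need for a treatment that the protocol does not allow.
- **Cast-arm check** (Trial schedule): "After 7 days, a clinical and X-ray control are performed in order to rule out secondary dislocation". The first Cooney score comes at 3 months.
- **Secondary endpoint**: a second reduction and a renewed K-wire osteosynthesis are listed as outcomes.
- **Size** (Number of patients): "A total of 742 patients shall take part, with 371 per group".

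**The concern.** A cast-arm child whose fracture shifts and who is then reduced or pinned no longer has the treatment that defines the arm. Taken together, the Treatment, Discontinuation criteria and Power calculation/analysis sections make it plausible that this child is discontinued and drops out of the only set on which the claim rests. If that happens at the day-7 check, the child has no Cooney score either and would also miss the second condition for the per-protocol set.

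Such exclusion would be related to outcome and would fall mainly on one arm. The terms used for the repeat-procedure endpoints presuppose a first procedure, so in the control arm a similar event appears to be followed as an outcome.

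The Discussion aims at a statement about casting as a strategy for children at presentation, one that avoids anaesthesia and pins. Success among children who were never converted answers a narrower question. The two answers differ whenever converted children fare worse.

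**Working it through.** **The plan's own figure.** The 742 cannot be reproduced from the article, which gives no expected rates, power or dropout. One assumed set that fits is 95% success in both arms, one-sided 0.025, 80% power and Farrington-Manning, which needs 334 per arm; with 10% dropout, 668/0.9 = 742.2. Other sets also come close. I use 95% as the main assumption for this reason only.

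**Inputs.** From the article: 371 per arm, margin 5 points, one-sided 2.5%, Farrington-Manning. Assumed: control success 95%; share x of the cast arm converted; success s in converted and q in unconverted cast children; no exclusions in the control arm.

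**Step 1: what exclusion does to the cast-arm rate.**

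- All randomised: (1 - x)q + xs
- Per-protocol: q
- Gain from exclusion: q - [(1 - x)q + xs] = x(q - s)

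With q = 95% and x = 5%:

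| s | Gain (points) |
|---|---|
| 0% (conversion counts as failure) | 4.75 |
| 50% | 2.25 |
| 80% | 0.75 |
| 95% | 0 |

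With q = 90% and s = 95% the gain is 0.05 × (90 - 95) = -0.25 points, so per-protocol is then slightly the stricter set. The sign depends only on whether converted children do worse than the others.

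**Step 2: false-claim rate at the margin.** Fix the true all-randomised cast rate at 95 - 5 = 90%. Then q = (0.90 - xs)/(1 - x). With x = 5%:

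| s | q | Per-protocol difference | Chance of claiming non-inferiority |
|---|---|---|---|
| 70% | 0.865/0.95 = 91.05% | -3.95 points | about 8% |
| 50% | 0.875/0.95 = 92.11% | -2.89 points | about 20% |
| 0% | 0.900/0.95 = 94.74% | -0.26 points | about 79% |

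The analysis of all randomised children gives about 2.5% in every row. I checked the last column in two ways. Simulation with a random number of conversions gave 7.6%, 19.5% and 78.7%. Exact enumeration with 352 cast children fixed (371 × 0.95) gave 7.4%, 19.3% and 78.8%. With s = 90%, equal to q, enumeration gives 2.4%, so there is no inflation.

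**Step 3: sensitivity to the assumptions.** With conversion counted as failure and the true difference again at -5 points, the per-protocol claim rate is:

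| Conversion | Control 95% | Control 90% |
|---|---|---|
| 1% | 6.5% | 5.3% |
| 2% | 16% | 11% |
| 3% | 33% | 20% |
| 5% | 79% | 50% |

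These are upper cases, because the article's endpoint does not score conversion as failure. The remanipulation rate in the Background concerns closed reduction, so it cannot stand in for the conversion rate in the cast arm.

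**The case against.** The strongest reply is that the exclusion is inferred. The article does not define a major protocol violation, and the full protocol or SAP may do so. Reduction and K-wire pinning are themselves protocol treatments, in the control arm; what the Treatment section expressly rules out is another form of osteosynthesis. The discontinuation criterion can therefore be read more narrowly. The repeat-procedure endpoints are not tied to an arm, and the cast-arm schedule foresees a course that is not uneventful. Control children who need a different osteosynthesis might be excluded too. All of this stands, and it is why the point is worded as a risk.

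A second reply is that per-protocol is a usual part of a non-inferiority trial, because keeping children who received control-type treatment in the cast arm can pull the arms together. That also stands. The weakness is that the per-protocol set decides alone.

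A reader might go further and infer that the test is biased towards success as a matter of fact. The documents do not support this: the bias is x(q - s), and they give neither the conversion rate nor the outcome of converted children. Nor is it fair to contrast about 84% (per-protocol) with 3% (all randomised, conversion as failure) at 95% success and 5% conversion. That changes the endpoint as well as the analysis set. On the stated endpoint the second figure would be 33%, 70% or about 85% if converted children succeed in 50%, 80% or 95% of cases. The composite difference there is -4.75 points, inside the margin, so a claim would not even be false.

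**Conclusion.** The point holds as a conditional weakness in a choice the article states. The only confirmatory test uses a set from which cast-arm children may be removed for a reason linked to outcome, and nothing in the claim rule guards against this. At 95% control success, 5% conversion and a true difference of exactly -5 points, the false-claim rate moves from the nominal 2.5% to about 8% or 20% if converted children succeed in 70% or 50% of cases. It reaches 79% only if conversion itself counts as failure. It does not rise if they do as well as the others. All rates are assumptions, as are the exclusion of every converted child and of no control child. An unseen SAP may add a supportive all-randomised analysis, but the claim as stated would still not depend on it. I rate this a cheap improvement, not a proven error in the result.

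**What to change.** 1. Claim non-inferiority only if the Farrington-Manning lower limit is above -5% in both sets: all randomised children analysed as allocated on the stated 24-month endpoint, and the per-protocol set.
2. Continue 24-month data collection for children who depart from the allocated treatment, so that discontinuation does not also remove the outcome.
3. State that a reduction or pinning after the allocated initial treatment is not in itself a reason for exclusion from the all-randomised set.
4. Add a sensitivity analysis that counts conversion as non-success. It belongs there and not in the primary analysis, because it changes the question from function and appearance at 2 years to success of a treatment strategy.

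The cost is a wording change, one extra analysis plus the sensitivity analysis, follow-up of any discontinued children, and slightly lower power because both sets must agree. If converted children do as well as the rest, the two sets taken singly have nearly the same power (about 84% and 85% at 95% success and 5% conversion). If they do worse, the all-randomised result is less favourable. The article reports 42 children included at submission, so the change could still have been made well before 24-month results.
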